### Recruitment

Patients with COVID-19 will be recruited at the participating clinical sites.

### Assignment of interventions: allocations

#### Sequence generation

Randomization among the two arms will be 1:1 and will be stratified per center.

The randomization process has been developed using the RERAND system integrated within the RDC Onsite ECRF system based on Oracle.

#### Concealment mechanism

This open-label trial will use blind randomization of patients in a 1:1 ratio to CP (+SOC) or SOC alone through a centralized system embedded in the eCRF (Oracle Clinical). Baseline clinical data will be entered in the eCRF before the patient can be randomly assigned via the eCRF at 1:1 ratio to receive standard of care with or without CP as add-on therapy. The system will automatically notify the assigned treatment arm at the eCRF screen and will send a confirmatory message at the email with the randomization information.

#### Implementation

Patients in the treatment arm will receive a single unit of CP (250–300 mL) after randomization on day 1 under control of the patient’s clinician and the Transfusion Service’s hematologist of the hospital.

Pathogen-reduced plasma bags will be frozen below − 25 °C and stored and shipped following European guidelines for blood components storage (36 months below − 25 °C or 3 months below − 18 °C). For transport, plasma bags must be kept frozen. No special containers are needed if plasma units are kept frozen at the delivery.

### Assignment of interventions: blinding

This is an open-label study. To reduce treatment bias, the eCRF did not allow randomizing a subject until sufficient clinical information from the subject was already included, reducing the possibility that a given subject could be re-randomized. Additional measures were implemented to reduce assessment bias, e.g., clinical information was collected, and daily clinical decisions were taken by the medical staff at each study center, that in most cases were not part of the research team. The primary endpoint was restricted to WHO scores ≥ 5 in an attempt to not only focus on relevant outcomes, but also to increase the robustness of the endpoint; although some scores are subjected to clinical judgment, these are hardly influenced by the clinical trial participation and/or treatment assignment.

### Data collection and management

#### Plans for assessment and collections of outcomes

Investigators are responsible for assessment and collection of outcomes, baseline, and other trial data. Data will be entered in the CRF by delegated team members and will be monitored by the clinical research associated. Subjects will be assessed daily while hospitalized. Patients discharged before the end of follow-up will be regularly phoned or asked to attend study visits. NP/OP swabs for virus analysis and blood samples for serological analysis will be sent to a central laboratory, where test will be performed according to laboratory standard operating procedures.

#### Plans to promote participants retention and complete follow-up

Patients are free to withdraw from participation in the study at any time. The decision must be communicated and reviewed by investigators. Staff at study sites should explain to these subjects the importance of staying in the study for the full duration of follow-up of this trial for safety reasons. The reason for patient discontinuation from the study will be recorded on the appropriate case report form.

In cases where that a patient becomes lost to follow-up, attempts to contact the patient should be made and documented in the patient’s medical records. Patients who withdraw from this study or are lost to follow-up after signing the informed consent form (ICF) and receiving the study product, will not be replaced.

#### Data management

Data will be examined for compliance with the trial protocol by the monitor and the data manager. Deviations will be sent to the project statistician to plan listings for the data review (DR). The objective is to carry out the population selection and definition of the final study populations as well as a preliminary assessment of the quality of the trial data.

All data will be recorded using the defined CRF guidelines for this trial. Also, the blood bank software in each hospital Transfusion Service will be used for recording the plasma units transfused.

#### Confidentiality

Subject confidentiality is strictly held in trust by the participating investigators, their staff, and the sponsor and their agents. This confidentiality is extended to cover clinical information relating to subjects, test results of biological samples, and all other information generated during participation in the study. All study data and research specimens that leave the site (including any electronic transmission of data) will be identified only by a coded number that is linked to a subject through a code key maintained at the clinical site. All source records including electronic data will be stored in secured systems.

No identifiable information concerning subjects in the study will be released to any unauthorized third party. Subject confidentiality will be maintained when study results are published or discussed in conferences. The study monitor, other authorized representatives of the sponsor, representatives of the Research Ethics Committees (RECs), and/or regulatory agencies may inspect all documents and records required to be maintained by the investigator, including but not limited to medical records (office, clinic, or hospital) for the subjects in this study. The clinical study site will permit access to such records.

#### Plans for collection, laboratory evaluation, and storage of biological specimens for genetic or molecular analysis in this trial/future use

Samples will be collected by investigators or designees. After that, handling, labeling, processing, storage, and/or shipping according to protocol will be performed and the samples will ultimately be sent to the central laboratory.

The Sponsor and the center may use data and samples for future research projects related with COVID-19, taking the appropriate measures to ensure the protection of their privacy and will not allow their encrypted data to cross with other databases that could allow their identification. Any future studies will be previously evaluated by a Research Ethics Committee and will comply with the applicable ethical and legal requirements.

### Statistical methods

#### Statistical methods for primary and secondary outcomes

A detailed Statistical Analysis Plan (SAP) agreed upon by the CT Executive Board and the Project Statistician will be available early during the recruitment phase. This SAP will follow the general regulatory recommendations given in the ICHE9 (CPMP/ICH /363/96) guidance, as well as other specific guidance on methodological and statistical issues [8].

Likewise, it will stick to the recommendations given by the consensus documents of the scientific journals to improve reliability and value of medical research literature by promoting transparent and accurate reporting of clinical research studies.

The proportion of patients with failure, defined as category 5, 6, or 7 of the 7-point ordinal scale at day 15, will be estimated using a log-binomial regression model including stratification variables. In the unexpected event that the model does not fit, the Poisson regression model with long-link and robust variance estimator will be used instead.

Binary efficacy and safety outcomes will be analyzed as described for the primary endpoint.

Kaplan-Meier model will be used to analyze survival endpoints (TTF and OS). In all these analyses, in addition to the Kaplan-Meier curve, median, Q1, Q3, and their corresponding 95% CI, number of events, and censored case distribution will be shown. Group comparisons will be done using the (stratified) log-rank test and the (stratified) hazard ratios (HR) (95%CI) from the Cox model.

##### Interim analyses

Interim analyses for comprehensive efficacy (or futility) and safety data monitoring analyses will be conducted when 20, 40, 60, and 80% of patients have been recruited and completed day 15 assessment, or at the discretionary criteria of the DSMB, when needed. The study may be stopped prematurely if either the efficacy or the futility boundaries are crossed. The boundaries will be adapted to the actual information rates in each inspection using the rho family spending functions (rho = 7) implemented in the East validated software v6.5 (or later releases) by Cytel Inc..

Ad hoc reviews will be undertaken at any time if there are other specific safety concerns. The study will not stop enrolment awaiting these DSMB reviews, though the DSMB may recommend temporary or permanent cessation of enrolment based on their safety reviews.

##### Methods for additional analyses (e.g., subgroups)

Subgroup analyses will be performed to assess the impact on efficacy of two different key factors, i.e., the level of neutralizing antibodies in the administered plasma and the timing of the disease, i.e., early or late stages considering 7 days as cut-off, viral load, and IgG or IgM. The following strategy will be conducted before splitting the analysis into subgroups: test of the overall treatment effect, test of the treatment-by-subgroup interaction at the 10% level of significance, or test of the treatment effect in each subgroup category.

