### Study interventions

#### Intervention description

All trial participants will receive SOC for COVID-19. The control arm is SOC for COVID-19. In the treatment arm, patients will also receive intravenous pathogen-reduced CP from patients recovered from COVID-19 (designated as donors) as add-on therapy to SOC.

In the current status of a worldwide pandemic for which we have no approved vaccines or drugs, for the purpose of this trial SOC will include any medicinal products being used in clinical practice (e.g., lopinavir/ritonavir; darunavir/cobicistat; hydroxy/chloroquine, tocilizumab, remdesivir, allowed as SOC when its use outside clinical trials was permitted), other than those used as part of another clinical trial.

Donor assessment, pathogen-reduced plasma collection, and production will be performed by hospital Transfusion Services and Regional Transfusion Centers. Local organization will be adapted to the existing structure at the regional level.

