Concerning the study population, a potential role of immunotherapy across the spectrum of COVID-19 disease has been suggested and several studies are ongoing to test different hypotheses. When defining the study population for our study, we considered that the best candidates for passive immunotherapy would be patients hospitalized due to COVID-19 pneumonia, thus in need for treatment, but early in the course of the disease when a primary immune response is not yet established. As a result, only patients requiring hospitalization for COVID-9 pneumonia without mechanical ventilation (invasive or non-invasive) or high flow oxygen devices, and with no more than 12 days between the onset of symptoms (fever or cough) and treatment administration day were allowed to enroll. It was believed that this early intervention would allow patients to benefit from the immune response of a subject who had developed a successful one, which might help clearing SARS-CoV-2 virus and to prevent progression to a more severe condition. On the other hand, patients requiring ventilation (mechanical or non-mechanical) were excluded given that they are less likely to respond to passive immunotherapy and more likely to develop ADE (antibody-dependent enhancement of disease), a worrisome complication seen previously in other viral infection [13] where a high specific antibody infusion could trigger a severe life-threatening immune response.

With regard to convalescent plasma donor’s selection, processing, and storage, it has been performed following the European and Spanish guidelines (RD 1088/2005) for standard plasma donation, including a pathogen reduction (PR) treatment. Lack of process control and standardization has been raised as one of the reasons why clinical trials have failed so far. We will select CP with anti SARS-CoV-2 IgG antibodies using a validated enzyme-linked immunosorbent assay (ELISA), with an IgG amount above a standardized cut-off. These assays have been performed at the trial central laboratory. No previous determination for neutralizing antibody titers will be used to select CP in our trial, as this would be the norm in the use of CP in the midst of a pandemic. Titration of neutralizing antibodies in the administered plasma will be subsequently performed and its relation to the outcomes could provide useful information about efficacy and safety of CP.

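### A treatment-by-subgroup interaction on the antibody level of the infused plasma cannot be estimated, because control patients receive no plasma

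*Protocol article*

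**What the plan says.** The section on additional analyses in the protocol article announces two key subgroup factors: "the level of neutralizing antibodies in the administered plasma", and disease timing with a 7-day cut-off. It then adds viral load and IgG or IgM. One strategy serves all of them: "The following strategy will be conducted before splitting the analysis into subgroups: test of the overall treatment effect", followed by "test of the treatment-by-subgroup interaction at the 10% level of significance, or test of the treatment effect in each subgroup category". No separate method is given for plasma titre.

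The rest of the article settles who can have a titre:

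- Intervention description: "The control arm is SOC for COVID-19".
- Implementation: "Patients in the treatment arm will receive a single unit of CP", given after randomisation.
- Discussion: "No previous determination for neutralizing antibody titers will be used to select CP in our trial".
- Discussion, on timing and purpose: "Titration of neutralizing antibodies in the administered plasma will be subsequently performed and its relation to the outcomes could provide useful information".

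**The concern.** A treatment-by-subgroup interaction asks whether the difference between the arms changes across levels of a factor. Each level must therefore contain patients from both arms. The titre of the infused unit is a property of the treatment. It comes into being after randomisation, and in one arm only.

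Titre is one of the two factors that the plan calls key, and the Discussion expects it to be informative about efficacy and safety. If the stated test is run, the model may not visibly fail. Software commonly drops one redundant column and prints a coefficient under the interaction label. Readers would take that number as randomised evidence that high-titre plasma works better or worse, when it is a comparison among treated patients only.

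A second, smaller matter is the word *or* in the testing strategy. As printed, no step is conditional on another, so it is unclear whether category-specific tests need a significant interaction, a significant overall effect, both or neither.

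**Working it through.** **Estimability**

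Let T = 1 for CP and 0 for control, and H = 1 for high-titre plasma and 0 for low. The interaction model has four columns: 1, T, H and T×H. The plan has 139 patients per arm (Sample size section).

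1. *Controls coded low (H = 0).* For controls H = 0 and T×H = 0. For CP patients T×H = H. So H and T×H are the same column, and the rank is 3 of 4.
2. *Controls coded high (H = 1).* For controls H = 1 and T×H = 0. For CP patients again T×H = H. So H = (1 − T) + T×H, and the rank is again 3 of 4.
3. *Controls left missing.* They drop out of the model. Only T = 1 remains, so T equals the constant and T×H equals H. The rank is 2.
4. *A factor measured in both arms,* such as days since onset. All four columns are distinct, and the rank is 4 of 4.

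In case 1 the three estimable quantities are the control level, low-titre CP against all controls, and high against low titre within CP. The last is the one that would carry the interaction label. Titre was not randomised, so it is an observational contrast.

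Numerical rank checks with 139 per arm give the same results: 3, 3, 2 and 4.

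**Information available for a titre analysis**

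At the 10% event rate assumed for the experimental arm, 139 × 0.10 = 13.9, or about 14 CP events. That supports very few model terms. Adjusting for centre alone, with 32 or 33 sites according to the article, is out of reach.

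**Effect of the *or***

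The plan gives no figure to reproduce. The following is an illustration under assumptions: two equal categories per factor, independent factors that can be split in both arms, category tests and the overall test at two-sided 5%, the interaction at 10%, and no treatment effect anywhere. The same patients are re-split by each factor, so tests on different factors are correlated.

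- *One factor, no gate.* The two categories are disjoint: 1 − 0.95² = 9.75%.
- *Both gates, k factors.* The overall and interaction statistics are independent under the null. If both are significant, the larger category statistic is at least (1.96 + 1.645)/√2 = 2.55, so it exceeds 1.96 automatically. The risk is 0.05 × (1 − 0.9^k): 0.5% for k = 1, about 1.0% for k = 2 and 1.7% for k = 4.
- *Remaining cases,* by simulation with 200,000 runs:

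| Factors | No gate | Interaction gate only | Both gates |
|---|---|---|---|
| 1 | 9.7% | 4.9% | 0.5% |
| 2 | 16% | 9.4% | 1.0% |
| 4 | 25% | 17.5% | 1.8% |

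The simulated both-gates column agrees with the formula to within about 0.1 percentage point.

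**The case against.** The strongest defence is that this is one factor caught in a generic sentence of a condensed article that leaves detail to an analysis plan not shown here. The Discussion already speaks of the relation between titre and outcomes, which is an exposure-response question. This bears on how easy the correction is. It does not rescue the text, because the article states a test for this factor that its own design cannot support. The exploratory outcomes do include neutralizing antibodies in a subset of patients at baseline, but that is a characteristic of the patient, not of the infused unit.

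Three stronger readings are tempting and should not be made:

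- *That the* or *removes all protection.* The sentence introduces the list as coming before any split and puts the overall test first. That points to a sequence, and *or* may be a slip. The wording is ambiguous; it does not show that ungated testing is intended.
- *That the false-positive risk is 34%.* That is 1 − 0.95⁸ = 33.7%, which treats eight subgroup tests as independent. Each factor re-splits the same 278 patients, and the risk is then about 25%. Nor is all of that due to the *or*: the interaction gate alone still leaves 17.5%.
- *That titre is known to follow donor pool, centre and calendar time.* Regional plasma collection, the recruitment pause and the later change in eligibility make this plausible, but the article reports nothing about how titre varied. Since neutralizing titre did not guide the choice of unit, deliberate matching of titre to patients is unlikely. The contrast is non-randomised; how confounded it is remains unknown.

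**Conclusion.** The main point holds. The interaction between treatment and plasma titre is not estimable under the stated design, whatever code is given to controls. This follows from the article's own description of the arms and needs no numerical assumption.

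The *or* is a secondary point of wording. Its size depends on assumptions the article does not fix: it gives a cut-off only for days since onset and no significance level for the category tests. The four-factor figures are therefore illustrative. They also treat every factor as splittable in both arms, which plasma titre is not.

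A reader might infer that the trial's main conclusion is at risk. It is not: these are additional analyses, and the primary endpoint analysis and the stopping boundaries do not depend on them. The correction should be made before results by titre are reported.

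**What to change.** 1. Remove plasma titre from the interaction and subgroup list.
2. Analyse it within the CP arm as an exposure-response relation, with log titre as a continuous variable, labelled non-randomised and exploratory. Prespecify only a few adjustments, for example baseline severity and enrolment period, given about 14 expected events.
3. Keep interaction tests for baseline factors measured in both arms: days since onset, viral load, and the patient's IgG or IgM.
4. Replace the *or* with an explicit sequence in the article's own order: overall effect; then interaction at 10%; then category-specific tests only if both earlier steps are met. Otherwise report subgroup estimates with intervals and no tests. Conditioning on the interaction alone would drop the overall test that the article lists first, and in the four-factor illustration would leave the risk at 17.5% rather than under 2%.

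The cost is a change of wording and no new data. The titre result can no longer be presented as a randomised subgroup effect, and with so few events the within-arm estimate will be imprecise.

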### Eligibility criteria

#### Eligibility criteria for patients

*Inclusion criteria are as follows:*
Written informed consent prior to performing study procedures. Witnessed oral consent will be accepted in order to avoid paper handling, which increased the risk of transmission of the infection. Written consent by patient or representatives will be obtained as soon as possible.Male or female adult patient ≥ 18 years of age at the time of enrolment.Laboratory-confirmed SARS-CoV-2 infection as determined by PCR in naso/oropharyngeal swabs or any other relevant specimen obtained in the ongoing COVID-19 symptomatic period. Alternative tests (i.e., rapid antigenic tests) are also acceptable as laboratory confirmation if their adequate specificity has been accepted by the sponsor.Patients requiring hospitalization for COVID-19 without mechanical ventilation (invasive or non-invasive) or high flow oxygen devices and at least one of the following:- Radiographic evidence of pulmonary infiltrates by imaging (chest X-ray, CT scan, etc.) OR- Clinical assessment (evidence of rales/crackles on exam) and SpO2 ≤ 94% on room air that requires supplemental oxygen.No more than 12 days between the onset of symptoms (fever or cough) and treatment administration day. Following 31 August amendment, only patients with no more than 7 days between the onset of symptoms and treatment administration day are allowed for inclusion.

*Exclusion criteria are as follows:*
Requiring mechanical ventilation (invasive or non-invasive) or high flow oxygen devices at screening.More than 12 days since symptoms (fever or cough) onset.Participation in any other clinical trial of an experimental treatment for COVID-19.In the opinion of the clinical team, progression to death is imminent and inevitable within the next 24 h, irrespective of the provision of treatments.Any incompatibility or allergy to the administration of human plasma.Stage 4 severe chronic kidney disease or requiring dialysis (i.e., eGFR < 30).

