An important issue in our trial is that we selected our CP donors from recovered mild COVID-19 conditions. Although patients recovered from severe COVID-19 was not an exclusion criteria for donors in our trial, we chose mild donors based in two assumptions: first, severe patients could have a high anti SARS-CoV-2 IgG titer, but low neutralizing antibody titers; second, high neutralizing antibodies titers in CP could increase the risk of ADE (antibody-dependent enhancement of disease). Thus, our donor selection strategy is aimed to select CP with medium levels of antibody titers, which is thought to provide a fair balance of efficacy and safety.

CP will be administered as an add-on to the standard of care as defined in each study center. Based on the clinical practice recommendations in place at the time the study was designed, the standard of care could be based on any of the following: lopinavir/ritonavir, darunavir/cobicistat, hydroxy/chloroquine, tocilizumab. Remdesivir was added to standard of care once it was available outside clinical trials. Demonstration of efficacy in this context is particularly challenging, but ethical and feasibility issues were prioritized.

Defining the primary endpoint posed additional challenges given the existing uncertainties around the natural course of the disease, and the need to balance hard clinically relevant outcomes against outcomes that might occur earlier. The ordinal scale recommended by the WHO for clinical trials in COVID-19 was finally selected, as it was considered to provide a reasonable balance between these two criteria, while facilitating any external comparison with similar clinical trial outcomes. We also include a range of secondary endpoints to assess the scope of the disease and the potential benefits/risks of treatment in a broader spectrum, in an attempt to show consistency and the robustness of any potential effect shown in the primary endpoint.

Finally, to overcome practical difficulties due to paper handling limitations at COVID wards but to still comply with ethical requirements applied to clinical research, oral witnessed consent will be accepted before entering the trial. Written consent form will be obtained from the patient himself or acceptable representatives as soon as possible.

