### Trial status

Patient’s recruitment started on 4 April 2020, under conPlas-19 Protocol version 2.2 as of 22 April 2020. Donor’s recruitment started on 2 April 2020. As of 10 July 2020, patients’ recruitment was temporarily interrupted awaiting some study modifications. By 31 August, the study design was amended to restrict the inclusion to patients with no more than 7 days of symptoms, and the follow-up was extended up to 60 days. ConPlas-19 Protocol version 3.3 as of 30 September 2020 is now in place, allowing the use of rapid antigenic tests as laboratory confirmation test for SARS-CoV-2 infection.. It is anticipated that recruitment will be complete by end of 2020.

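### Since the 31 August amendment the 7-day entry limit equals the 7-day subgroup cut-off, so the early/late treatment interaction is partly confounded with enrolment period

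*Protocol article*

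**What the plan says.** The section on additional analyses names two key factors for subgroup analysis: the neutralising antibody level of the plasma, and "the timing of the disease, i.e., early or late stages considering 7 days as cut-off". The strategy includes a "test of the treatment-by-subgroup interaction at the 10% level of significance".

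The patient eligibility criteria give two successive symptom windows. The first is "No more than 12 days between the onset of symptoms (fever or cough) and treatment administration day". The second applies after the amendment: "only patients with no more than 7 days between the onset of symptoms and treatment administration day are allowed for inclusion". Trial status repeats this ("By 31 August, the study design was amended to restrict the inclusion to patients with no more than 7 days of symptoms"). It also says that patient "recruitment started on 4 April 2020" and was interrupted as of 10 July 2020 pending study modifications.

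The document describes other changes over time. On background care it says: "Remdesivir was added to standard of care once it was available outside clinical trials". Trial status adds that protocol version 3.3 of 30 September 2020 allows rapid antigen tests for laboratory confirmation.

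Randomisation is 1:1 and stratified by centre only. The primary model is log-binomial with the stratification variables, and other binary outcomes follow it. The subgroup section mentions neither an enrolment-period term nor a restriction to patients enrolled while both symptom windows were open.

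**The concern.** An early/late interaction is informative about timing only if the two strata are otherwise comparable in what could modify the treatment effect. Here the amendment closed one stratum and left the other open. From then on every new patient adds to the early stratum and none to the late one, so the contrast sets a first-period-only group against a mixed-period group.

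Timing is one of two factors that the plan singles out, and the Background and Discussion both argue for giving plasma early. An interaction found here would be taken as evidence on that question. If it partly reflects a change in plasma's relative effect between spring and autumn 2020, the trial could report a timing effect that does not exist or miss one that does.

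**Working it through.** The plan gives no figure on this point. The structural argument needs only the eligibility text; the size needs assumptions, labelled as such below.

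**1. Which cells can be filled.**

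| | Up to 7 days (early) | More than 7 days (late) |
|---|---|---|
| Before the amendment (limit 12 days) | open | open |
| After the amendment (limit 7 days) | open | empty by eligibility |

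The exclusion list still gives the 12-day limit, but the amended inclusion criterion is the binding one. The article does not say on which side day 7 falls. If day 7 counted as late, some post-amendment patients would enter the late stratum, and the imbalance would be smaller but not gone.

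**2. How a period difference enters.** Let f be the share of patients enrolled before the amendment and l the late share among them. The first-period share of the early stratum is

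w = f(1 − l) / [f(1 − l) + (1 − f)].

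The document gives neither f nor l. Assume f from 0.4 to 0.8 and l from 0.3 to 0.7:

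- f = 0.4, l = 0.7: w = 0.12 / 0.72 = 0.17.
- f = 0.8, l = 0.3: w = 0.56 / 0.76 = 0.74.

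In both scenarios below timing has no effect at all.

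**Scenario A (assumed):** risk ratio 1.0 before the amendment and 0.5 after, equal control rates. The late risk ratio is 1.0. The early risk ratio is w × 1.0 + (1 − w) × 0.5, which is 0.58 at w = 0.17 and 0.87 at w = 0.74. The midpoint case f = 0.4, l = 0.5 gives w = 0.20 / 0.80 = 0.25 and 0.25 + 0.375 = 0.625. Early treatment looks better.

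**Scenario B (assumed):** 20% control versus 10% plasma before; 12% in both arms after. The late risk ratio is 0.50.

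- w = 0.17: early = (0.167 × 0.10 + 0.833 × 0.12) / (0.167 × 0.20 + 0.833 × 0.12) = 0.1167 / 0.1333 = 0.88; ratio to late 1.75.
- w = 0.74: early = 0.1053 / 0.1789 = 0.59; ratio to late 1.18.

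Late treatment looks better. In both scenarios, restricting to first-period patients returns a ratio of exactly 1.00.

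**3. What does not create the artefact.** Suppose the control risk changes from c1 to c2 but the risk ratio r is the same in both periods. The early risk ratio is then r(w·c1 + (1 − w)·c2) / (w·c1 + (1 − w)·c2) = r. On the risk-ratio scale of a log-binomial model, a proportional shift in background risk leaves the interaction alone. Only a treatment-by-period difference distorts it.

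**4. Whether period terms would rescue the pooled data.** Fit treatment, timing, period, treatment-by-timing and treatment-by-period. Because the late/post-amendment cell is empty, the post-amendment patients are fully described by the period and treatment-by-period terms. Apart from shared centre effects, the treatment-by-timing term is estimated from first-period patients alone. The two approaches are equivalent for identifying timing.

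**5. Power.** Take f = 0.4, l = 0.5: 0.4 × 278 = 111 first-period patients, about 28 per arm in each timing stratum. Assume control risk 20%, halved by plasma in early patients only. The variance of the log ratio of risk ratios is the sum of (1 − p)/(np) over the four cells.

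- First period only: 3 × 0.8/5.6 + 0.9/2.8 = 0.75; SE 0.87; ln 2 / 0.87 = 0.80. Power at the two-sided 10% level is about 21% by normal approximation. Simulation, which reflects the sparse cells, gives about 15%.
- All 278 pooled: 0.8/22.2 + 0.9/11.1 + 2 × 0.8/5.6 = 0.40; SE 0.63; ln 2 / 0.63 = 1.09. Power is about 29%, valid only if there is no treatment-by-period difference.

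**The case against.** The best case against has five parts.

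- **No evidence that the relative effect changed.** The document gives no date for remdesivir, which may have entered standard care within the first period. Antigen tests came with the 30 September version, a month after the eligibility change, and nothing suggests that they alter plasma's relative effect. This stands: a period difference is possible, not shown.
- **The test would usually not fire.** In scenario A with f = 0.4, l = 0.5 and an assumed 20% control risk, simulation of a Wald test at the 10% level flags the interaction about 18% of the time, against about 8% with no effect anywhere. This stands as to size. It does not remove the misattribution in the estimates.
- **The remedy discards information.** This mostly fails. Post-amendment patients have no late comparators, so they tell us about timing only if period is assumed not to matter.
- **The SAP may deal with it.** It may. But the article fixes the subgroup, cut-off and test, describes the amendment, and leaves the subgroup unadapted.
- **It is an additional analysis in a phase 2 trial.** True, and it limits the weight of the point.

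A reader might also infer that the primary model is wrong because it ignores the change in population. The document does not support that: allocation is 1:1, concurrent and stratified by centre, and a change in eligibility does not bias that contrast. Nor does it support reading the amendment as driven by evidence on timing; Trial status gives no reason for it, and the early-treatment rationale in the Discussion is attached to the 12-day limit.

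**Conclusion.** The point holds for the early/late interaction. That late patients come only from the first period follows from the eligibility text, with up to 7 days read as early, and needs no assumption about numbers. The confounding is partial, because early patients were also enrolled in the first period.

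The size and direction of any bias cannot be derived from the document. The ranges above rest wholly on assumed splits and assumed, rather strong, period effects, and they point opposite ways. It would be tempting to say that the plan will manufacture evidence for early treatment; scenario B shows that it could equally favour late treatment. It would also be too strong to say that any change in background care is enough, since step 3 shows that a proportional shift in risk is harmless.

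The treatment effect within each stratum, and the primary comparison, remain valid randomised contrasts. What is unsafe is attributing the early/late difference to timing. This should be corrected before the subgroup analysis is run, but the primary conclusion does not depend on it.

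**What to change.** In the section on additional analyses:

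1. Estimate the treatment-by-timing interaction in patients randomised before the 31 August 2020 amendment, when both strata were open. Alternatively, use all patients with period and treatment-by-period terms.
2. Report the treatment effect in post-amendment patients as a separate period estimate.
3. If a pooled early/late comparison is still shown, label it as not separating timing from period.
4. State on which side of the cut-off day 7 falls.

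Days since onset as a continuous term, within the first-period patients, is optional. No change to the primary model is needed.

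This is a wording change and needs no new data. The price is precision: with the assumed 40% to 80% enrolled before the amendment, the timing test rests on about 111 to 222 of 278 patients (0.4 × 278 and 0.8 × 278). At the lower end it has the low power shown in step 5. The text should therefore say that a non-significant interaction is not evidence that timing is irrelevant.
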